## Abstract

**Background:**

Syphilis is a common sexually transmitted infection (STI) among men who have sex with men (MSM). Increasing syphilis testing is important to syphilis control. However, in low- and middle-income countries like China, syphilis testing rates remain low among MSM. We describe a randomized controlled trial protocol to examine the effectiveness of social network distribution approaches of syphilis self-testing among MSM in China.

**Methods:**

We will recruit index and alter MSM. Indexes will be eligible if they: are born biologically male; aged 18 years or above; ever had sex with another man; are willing to distribute syphilis testing packages or referral links to their alters; and willing to provide personal contact information for future follow-up. Three hundred MSM will be recruited and randomly assigned in a 1:1:1 ratio into three arms: standard of care (control arm); standard syphilis self-testing (SST) delivery arm; and referral link SST delivery arm. Indexes will distribute SST packages or referral links to encourage alters to receive syphilis testing. All indexes will complete a baseline survey and a 3-month follow-up survey. Syphilis self-test results will be determined by photo verification via a digital platform. The primary outcome is the mean number of alters who returned verified syphilis testing results per index in each arm.

**Discussion:**

The trial findings will provide practical implications in strengthening syphilis self-testing distribution and increasing syphilis testing uptake among MSM in China. This study also empowers MSM community in expanding syphilis testing by using their own social network.

**Trial registration:**

Chinese Clinical Trial Registry, ChiCTR2000036988. Registered 26 August 2020 - Retrospectively registered.

**Supplementary Information:**

The online version contains supplementary material available at 10.1186/s12879-021-06137-0.

## Background

Syphilis remains a global health priority. The WHO estimated that the prevalence of syphilis among men who have sex with men (MSM) is 5% or more in at least 42 countries in 2018 [1]. From 2006 to 2012, the incidence of syphilis was 9.6 per 100 person-years among MSM living in China [2]. However, in low- and middle-income countries (LMICs) like China, syphilis testing rate is low among MSM. Studies showed that less than 30% of Chinese MSM has ever received a syphilis test [3].

Facility-based testing for syphilis has potential limitations related to stigma from providers [4], infrastructure requirement, inconvenience [5], and lack of privacy [6]. Recent advances in diagnostics such as self-testing, have enabled decentralized testing strategies [7] which makes testing more accessible. Syphilis self-testing is a process whereby an individual collects their own specimen, performs the test and interprets the result by themselves [3]. Several point-of-care syphilis tests have been approved and used for syphilis screening in China [8, 9]. A cross-sectional study showed that syphilis self-testing among MSM could complement facility-based testing in China [3]. Approximately half of the MSM reported that syphilis self-testing was their first syphilis test, suggesting that this could expand test uptake among groups without a history of testing [3]. A recent randomized control trial reported that syphilis self-testing significantly increased syphilis testing among Chinese MSM with less cost per person tested compared to facility-based testing [10]. With the potential benefits of syphilis self-testing, further studies are needed to explore how this could be scaled up.

Social network distribution can be an effective syphilis self-testing distribution strategy to expand syphilis testing and to reach high-risk populations with undiagnosed syphilis. This strategy allows participants (defined as indexes) to apply for multiple self-testing kits and distribute to their peers (sexual partners or non-sexual partners, defined as alters) within their social network [11, 12]. Social network distribution has been widely used for sexual partner notification with notification cards, which helps contain the spread of sexually transmitted infections (STIs) [13, 14]. However, this strategy is likely to reach only a proportion of contacts. For example, it is more successful in reaching partners in long-term relationships and less so in reaching short-term casual sexual contacts [14, 15]. Social network distribution of self-testing may be an effective approach to overcome these barriers [16]. A study showed that social network testing enables people at high risk for HIV or people living with HIV to encourage people in their social network to test for HIV [17]. This strategy is highly acceptable among MSM because it is distributed by trusted community leaders [18]. Social network distribution may reduce health disparities by decreasing barriers such as stigma and discrimination in health facilities [19], concerns for lack of confidentiality [20], and fear of sexuality disclosure [21] among hard-to-reach populations [17]. Given the feasibility of this strategy in expanding HIV self-testing among MSM, there is value in exploring whether this distribution strategy could also expand syphilis self-testing.

This study aims to examine the effectiveness of social network distribution approaches of syphilis self-testing through a three-arm cluster randomized controlled trial (cRCT) in Guangdong, China and to explore which approach could increase syphilis testing among Chinese MSM.

## Methods

### Study design

This is a non-blinded and parallel three-arm cluster randomized controlled trial among MSM living in China. Enrolled indexes will be randomly assigned in a 1:1:1 ratio into three arms: standard of care arm (control arm); standard SST delivery arm; and referral link SST delivery arm (referral link is used to apply for free SST packages). Indexes in the control arm will receive information packages with peer notification cards to encourage their alters to take a free syphilis screening at a designated health facility. Indexes in the standard SST delivery arm will receive free packages containing a SST kit to distribute to their alters. Indexes in the referral link SST delivery arm will be provided with SST referral links to distribute to their alters to access free syphilis self-testing packages online. Indexes in each arm will be followed up for 3 months (Fig. 1). The hypothesis in this study is that standard and referral link syphilis self-testing social network delivery model are more effective than standard of care among Chinese MSM. Preliminary data from pilot study will be used to inform the final trial design. Preliminary pilot results are available on the Supplement materials.

**Fig. 1 Fig1:**
[figure not shown]
Scheme of study design

### Study setting and population

All indexes will be recruited by health workers at local MSM voluntary counselling and testing (VCT) clinics (in Foshan and Dongguan) or community-based organizations (CBOs) (in Shenzhen) from three cities in Guangdong Province, China. All sites are run by MSM community-based organizations (Xinghuo LGBT center, Shenzhen; Friends Care Center, Foshan; and Rainbow Center, Dongguan) and provide free HIV/STI screening and consultations for MSM. The staff at each site has rich experience with counselling, blood collection, rapid testing for syphilis, results reporting, and follow up of syphilis tests. All sites will follow the same study procedures.

Indexes will be eligible if they are: born biologically male; aged 18 years or above; ever had sex with another man; are willing to distribute syphilis testing packages or referral links to their alters; and willing to provide personal contact information for future follow-up. All participants need to sign an electronic informed consent before they fill out the baseline survey. Considering MSM living with HIV might be at higher risk of syphilis, we increase awareness of syphilis for MSM with HIV and mobilize health workers to include as many indexes with HIV as possible in the recruitment stage.

### Arms and interventions

Arms and interventions are summarized in Table 1.

**Table 1 Tab1:** Group information

Arm	Intervention	Intervention delivery
**Standard of care arm**	1. **Information card**: the risk of acquiring syphilis, the importance of screening for syphilis, resources of three local syphilis test and linkage to care service sites, and a link of national syphilis VCT sites. 2. **Peer notification card**: social network distribution of notification card and encouragement of syphilis testing. 3. **Result report card**	1. Each index will receive 3 information packages at enrollment, and distribute packages to 3 alters. Maximum **ONE** package per alter. 2. Each alter who returns his testing result and completes a survey can receive 3 USD and his matched index will also receive an extra 3 USD. 3. Each index can apply for additional 3 packages when all his 3 alters return testing results. 4. Each eligible “secondary index” can apply for 3 information packages to distribute to his alters.
**Standard SST delivery arm**	1. **Information card**: the risk of acquiring syphilis, the importance of screening for syphilis, resources of three local syphilis test and linkage to care service sites, and a link of national syphilis VCT sites. 2. **SST kit package**: social network distribution of SST kit package and encouragement of SST. 3. **Result report card**	1. Each index will receive 3 SST packages at enrollment, and distribute packages to 3 alters. Maximum **ONE** package per alter. 2. Each alter who returns his testing result and completes a survey can receive 3 USD and his matched index will also receive an extra 3 USD. 3. Each index can apply for additional 3 packages (refundable deposit 3 USD/package) when all his 3 alters return testing results. 4. Each eligible “secondary index” can apply for 3 SST packages (refundable deposit 3 USD/package) to distribute to his alters.
**Referral link SST delivery arm**	1. **Information card**: the risk of acquiring syphilis, the importance of screening for syphilis, resources of three local syphilis test and linkage to care service sites, and a link of national syphilis VCT sites. 2. **SST referral link**: social network distribution of SST referral links and encouragement of SST. 3. **Result report card**	1. Each index will receive 3 SST referral links at enrollment, and distribute links to 3 alters. Maximum **ONE** link per alter. 2. Each alter can apply for **ONE** SST package through the referral link, and SST package will be posted to him free of charge. 3. Each alter who returns his testing result and completes a survey can receive 3 USD and his matched index will also receive an extra 3 USD. 4. Each index can apply for additional 3 referral links when all his 3 alters return testing results. 5. Each eligible “secondary index” can apply for 3 SST referral links to distribute to his alters.

#### Standard of care arm (control arm)

Each index MSM will initially receive three information packages to distribute to his alters after completing their baseline survey. Each information package contains: 1) a health promotion and linkage to care information card; 2) a crowdsourced peer notification card; and 3) a syphilis testing result report card. Crowdsourcing is a practice in which a group solves a problem and then shares the solutions with the community [22]. Peer notification contains healthcare provider location and index information, which each alter can use to receive a free syphilis screening in a list of nearby facilities for each study site. Each alter can use a maximum of one package and take one free facility-based syphilis testing service through peer notification card from each index.

#### Standard SST delivery arm

Index MSM in this arm will initially receive three SST packages to distribute to his alters after completing their baseline survey. Different from the information package for the control arm, we will give them SST kits instead of the peer notification card. Each SST kit contains equipment for blood sample collection, quick syphilis test and a step-by-step pictorial instruction for using the self-test kit. Each alter can use a maximum one SST package and take syphilis self-testing service from each index. In this trial, we will use the syphilis SD Bioline Syphilis 3.0 rapid test kit. The sensitivity and specificity for syphilis range 85.7–100% and 95.5–99.4% respectively [16, 23].

#### Referral link SST delivery arm

Index MSM in this arm will initially receive a unique SST referral link, which can be shared with up to three alters after baseline survey. Each link will expire after three times of usage. Each alter can only apply for one SST package with the link, which can be accessed by only one device (both a Wechat account and a phone number). Further, the SST package will be posted to the alter free of charge (free express delivery).

In all three study arms, each package or link will be assigned with a unique number for future returned results tracking and index matching. Alters will receive 3 USD when they send a photo verification of their self-testing or facility-testing results and complete the alter survey. Their matching index will also receive an extra 3 USD as incentive of successful distribution. In addition, each index can apply for additional three packages (refundable 3 USD deposit for each SST package; free of charge for notification card package) or for additional free referral links when their initial link has been used by three alters returning their test results. Further, each alter in all three arms who returned his result can become a “secondary index” if he is willing to and meets the following criteria: born biologically male, aged 18 years or above, and ever had sex with another man. He can also apply for three packages (refundable 3 USD deposit for each SST package; free of charge for information package) or referral link to distribute to his alters. For all indexes and alters in the study, researchers will provide a 24/7 hotline and online counselling.

### Randomization and allocation

At each site, eligible indexes will be assigned to one of the three arms through a cluster randomization procedure with ten participants per cluster. To ensure equal number of clusters in each of the three arms, the clusters will be randomized in a block of three at each study site. Computer-generated randomization codes will be produced and kept by a biostatistician who is not involved in participant enrollment. Ten blocks will be generated in total. Each block has three clusters consisting of standard of care arm, standard SST delivery arm, and referral link SST delivery arm, randomly created from all possible permutations. The schedule will be determined before the start of the study and then provided to each site. Each eligible index who presents to the site during a given 10-person cluster will be provided the allocated program. To reduce contamination between groups, eligible indexes will be allocated into the same group if they come in pair.

### Blinding

As it would not be possible to blind researchers and participants to participants’ group assignments, this is a non-blinded study.

### Follow up

The follow-up survey will be administered 3 months after recruitment for indexes. Each index will receive 4 USD after completing the follow-up survey. Any alters with a reactive self-testing results will be referred to undergo free confirmatory laboratory testing and clinical examination at study clinics or other local designated clinics/hospitals. If the participants are diagnosed with syphilis, we will undertake further follow-up to obtain treatment information. Alters with a reactive result who also return photo verification of confirmatory testing results or treatment proof will receive a further 3 USD. Alters with reactive results who do not return any proof for confirmation testing or treatment will be asked about further linkage to care information at the end of study.

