### Data collection

#### Syphilis testing record and results

All indexes’ information will be recorded using online surveys (Wenjuanxing online survey platform). Alters can photograph and upload their testing results to an online social media platform “WeChat” (instant messaging service/application) by scanning the QR code in the result report card. Syphilis testing results can be either from facility-based testing or self-testing.

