### Statistical methods

#### Sample size

We used an inequality test to calculate the sample size (PASS 15.0, NCSS, LLC). The details of the sample size calculation are shown in Table 2. Preliminary study results from the pilot RCT showed that the number of alters by an index was 0.05 through standard of care delivery, 0.60 through standard SST delivery, and 0.45 through SST link delivery. Based on the above data, we assumed that the variances of the three groups were equal with the same standard deviation of 0.8. Assuming the number of clusters will be allocated 1:1:1 to each arm, with cluster size of 10 per cluster, alpha of 0.05, power of 0.8, inter class correlation of 0.01, lost to follow-up rate of 0.20, we will need a minimum of 10 clusters per arm. To integrate the sample size calculations and to consider practicality, the final sample size would be ten clusters in standard SST delivery arm, ten clusters in SST referral link delivery arm, and ten clusters in standard of care arm, with a total cluster size of 30 (300 participants).

**Table 2 Tab2:** Sample size calculations

**SST and standard of care**	ICC	0.01
	Mean difference	0.55
	Standard deviation	0.8
	COV of cluster sizes	0.65
	Number of people per cluster	10
	Alpha	0.05
	Power	0.8
	Total sample size per arm	60
	Number of clusters per arm	6
**LINK and standard of care**	ICC	0.01
	Mean difference	0.4
	Standard deviation	0.8
	COV of cluster sizes	0.65
	Number of people per cluster	10
	Alpha	0.05
	Power	0.8
	Total sample size per arm	80
	Number of clusters per arm	8

*ICC* Intra-class correlation, *COV* Coefficient of variation

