Several challenges might emerge in the implementation of this study. First, adverse events such as forced testing, physical and verbal abuse among participants, being misunderstood during the delivery procedures may occur. The findings of these questions will provide insights to design better syphilis self-testing support. Second, existing intervention delivery cannot guarantee all three packages or links are distributed. To encourage distribution, indexes will receive 3 USD for each successful distribution. In addition, we will try to understand why indexes fail to distribute any or partial packages via our survey. This information will help to improve current distribution models. Third, we ask for a refundable deposit in the SST arm if indexes wish to apply for SST packages again or secondary indexes wish to apply for SST packages. This might greatly discourage participation. For future studies, we need to discuss whether or not we should keep using this refundable deposit or adjust the amount if recruitment needs to be expanded. Lastly, though we used an objective measure for our primary outcome (photo verified syphilis testing results), there is a possibility that we underestimate the number of alters testing for syphilis if they don’t upload their testing results. We try to mitigate this by offering alters monetary incentives after their testing result is verified by a research assistant.

There are some limitations in this study. First, recruitment takes places in specialist hospitals and local CBOs. This will exclude individuals who are less likely to attend these recruitment sites, leading to sample bias. Second, we use data from treponemal test results, which might overlook testers’ treatment history and clinical data that help differentiate new and old cases.

In conclusion, this study will provide data on optimizing syphilis self-testing programs to increase syphilis testing uptake and earlier syphilis diagnosis among MSM in China.

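### After the initial referral, the only study contact stated for reactive alters who return no proof is a linkage question at the end of study, not timed to the man's own result

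*Protocol article*

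**What the plan says.** The Follow up section of the protocol article sets out four steps for a reactive result.

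1. Alters with a reactive self-test "will be referred to undergo free confirmatory laboratory testing and clinical examination at study clinics or other local designated clinics/hospitals". No time is given for this referral.
2. "If the participants are diagnosed with syphilis, we will undertake further follow-up to obtain treatment information". This step depends on a diagnosis.
3. Photo proof of confirmation or treatment earns a further 3 USD.
4. Reactive alters who do not return "any proof for confirmation testing or treatment will be asked about further linkage to care information at the end of study".

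Other sections add support. The packages include a card with linkage-to-care information (Table 1). For all indexes and alters, "researchers will provide a 24/7 hotline and online counselling" (end of the section on the referral link arm). Site staff are described as experienced in "rapid testing for syphilis, results reporting, and follow up of syphilis tests" (Study setting and population).

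On the flow of results, alters can photograph and "upload their testing results to an online social media platform", namely WeChat (Syphilis testing record and results). The Discussion refers to "offering alters monetary incentives after their testing result is verified by a research assistant", so a member of the study team looks at each uploaded result before payment.

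**The concern.** The trial puts self-tests in the hands of men outside a clinic. A reactive result there is a screening result and needs confirmation and a clinical history. The article's own limitations say that a treponemal result can miss the treatment history and clinical data that separate new from old cases.

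Reactive alters who send no proof are the men whose care is unknown to the study. Some will have been treated and simply not sent a photo; others will not have attended. A question at the end of study can record which is which. A question asked a few weeks after the result could also prompt those who have not attended. For this group the article fixes the late question and states no earlier one.

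What is at stake is the care of a small number of men. Linkage to care is not among the listed primary or secondary outcomes, and the primary comparison is untouched.

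**Working it through.** The article states no figure on this point, so there is none to reproduce. The check has two parts: a comparison of the sections, and a count of the men involved.

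**Which contacts could reach a reactive alter who sends no proof?**

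| Step | Who starts it | Reaches a man who sends no proof? | Timed to his own result? |
|---|---|---|---|
| Referral to free confirmation (Follow up) | Study | Yes, if self-tested | It follows from his result; timing not stated |
| Follow-up for treatment information (Follow up) | Study | Only if he is diagnosed and the study learns of it | No time stated |
| Payment for proof (Follow up) | Alter | Only if he acts | No |
| Linkage-to-care card, hotline, online counselling | Alter | Only if he acts | No |
| Alter survey (Alter survey) | Study | Yes, but it is sent right after the upload | At upload only |
| 3-month survey (Follow-up survey) | Study | No, it is for indexes | No |
| Linkage question (Follow up) | Study | Yes | No, end of study |

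The alter survey accompanies the upload, so it cannot show whether he later attended. Between referral and the end of study, no section states a recontact of men without proof.

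**How many men?**

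Inputs:
- Indexes per arm: ten clusters of ten = 100 (Sample size).
- Alters per index in the pilot: "0.60 through standard SST delivery, and 0.45 through SST link delivery", and 0.05 in the control arm (Sample size).
- Positivity among testers: not given. Assumed 5% to 20%. The lower end matches the WHO figure of 5% or more in the Background; the upper end is an assumption.

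Expected self-testing alters = 100 × 0.60 + 100 × 0.45 = 60 + 45 = 105.

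Reactive self-testers = 105 × positivity:
- 5%: 5.25
- 10%: 10.5
- 15%: 15.75
- 20%: 21

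The control arm would add 100 × 0.05 = 5 facility testers, and so 5 × 0.05 = 0.25 to 5 × 0.20 = 1 reactive man.

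The range can be cross-checked with the test performance quoted in the section on the standard SST arm (sensitivity 85.7–100%, specificity 95.5–99.4%) and an assumed true prevalence of 5% to 10%. Reactives = N × p × Se + N × (1 − p) × (1 − Sp).
- Lowest: 105 × 0.05 × 0.857 + 105 × 0.95 × 0.006 = 4.50 + 0.60 = 5.1.
- Highest: 105 × 0.10 × 1.00 + 105 × 0.90 × 0.045 = 10.50 + 4.25 = 14.75.

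Both lie close to or inside the 5 to 21 range.

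The share without proof is not given. If it were 30%, the men to recontact would number 5.25 × 0.30 = 1.6 to 21 × 0.30 = 6.3. If it were 100%, they would number 5.25 to 21.

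These counts are not a ceiling. Additional packages and secondary indexes (section on the referral link arm) could add testers, and the WHO figure is itself a lower bound.

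**The case against.** The strongest reply is that the article is a condensed account. It does not say that the end-of-study question is the first or only contact after referral, and reminder schedules are the kind of operational detail left to the full protocol. Experienced site staff may well call these men sooner. The article also provides several layers of support: free confirmation, a payment, a card, a hotline, counselling, follow-up of diagnosed men and a final check. On this view, one more reminder is a matter of preference.

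Part of this stands. It rules out calling the text an error, and it rules out any claim that staff make no earlier contact. It does not remove the point, because the article is not silent on this group. It gives them a time, the end of study, and that time is a poor one for prompting care.

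Two stronger readings are tempting and are not supported:

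- A reader might infer that the end-of-study question is the study's only action for these men. The referral to free confirmatory testing is also a study action; it follows from the man's own reactive self-test and covers those who later send nothing. The point holds only for contact after that referral.
- A reader might want to say how many weeks too late the question comes. The documents do not define the end of study for an alter, do not say how uploads spread over the 3 months, and do not say how quickly results are verified. No delay in weeks can be derived from them.

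It might also be said that a recontact changes nothing in the analysis. That is too generous. Secondary outcomes include the average cost per syphilis diagnosis, and the Economic evaluation section divides costs by cases diagnosed and counts staff time. If a diagnosis there means a confirmed case, a recontact that works would slightly raise both diagnoses and personnel cost. The effect would fall mostly in the two self-testing arms, where 60 and 45 testers are expected against 5 in the control arm.

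**Conclusion.** The point holds as a cheap patient-safety improvement. After the initial referral, the only study-initiated contact the article states for reactive alters without proof is a linkage question at the end of study. It is not tied to the man's result and may come too late to prompt care.

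About 5 to 21 reactive self-testers are expected, resting on the pilot means, 100 indexes per arm and an assumed positivity of 5% to 20%. Only those without returned proof would need recontact, and that share is unknown. Men who had care but sent no photo would gain little.

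The documents do not support reading this as a missing safety net, as evidence that men go untreated, or as a threat to the primary result. Confidence is medium, because the full protocol may already provide an earlier contact.

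**What to change.** If no proof has arrived at a fixed interval after a reactive upload is verified, send the man one WeChat message with the linkage question. An interval of 2 to 4 weeks would be reasonable; this is a reviewer's choice, not a figure from the article. Apply the same rule in all three arms and to alters of secondary indexes. Keep the end-of-study question as a catch-up.

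The cost is a few messages and a little staff time for some or all of roughly 5 to 20 reactive men, possibly somewhat more with extra packages and secondary indexes. The upload channel and the verifying staff already exist. Record the recontact time as personnel cost in each arm, and say in the economic evaluation whether a diagnosis means a confirmed case, since that is where a small change could appear. The primary outcome, sample size and primary analysis stay as they are.
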